## 3.2 Prior studies and development of the medical device

### 3.2.1 Prior research

This project builds on the knowledge and experiences obtained from Sophia Step Study, a three-armed randomized controlled trial evaluating self-monitoring of physical activity and additional counselling as support for self-management of physical activity (17, 18). A process evaluation showed high adherence to the interventions at twelve months and that applying digital self-monitoring to support physical activity was feasible both with and without counselling support. No reverse effects were reported (19). The interventions were effective in increasing physical activity after six months, and in maintaining physical activity over two years (18). Though, the results showed a large individual variation, both in baseline physical activity patterns and in the level of change in physical activity. An interview study revealed that the participants were appreciative of the personalized approach of the program, receiving feedback on health outcomes and positive reinforcement (20). Participating in the research study led to a reported increase in awareness and motivation for physical activity, establishment of new routines, and a feeling of control over the own health (20). Some frustration was expressed concerning the reliability of the pedometer in measuring steps accurately (20). These above-mentioned findings point to the importance of an individual approach, targeting individual circumstances, needs, and preferences.

### 3.2.2 Formative evaluation

Prior to this clinical investigation, an intervention planning phase was conducted based on a framework for developing behavioral interventions (21) and a guide to developing and planning digital interventions (22). This formative evaluation phase included a systematic review of users' perceptions of e- and mHealth services promoting physical activity and healthy diets (2). In addition to the systematic review, two qualitative studies have been carried out. One study explored users' and health care professionals' perspectives on e-health and technology as a support for physical activity in diabetes self-management (23). The other study explored health care professionals' views on supporting physical activity in primary care (24). The findings from the systematic review and the two qualitative studies served as the basis for the development of the digital service to be evaluated (the app LongLife Active). Figure 2 shows an illustration of the development phases of the research project.

Figure 2. The three phases of the overall research project and parallel activities by the product developers. The first two research phases comprised the development of the digital service and the third phase includes evaluation of the product when on the market.

### 3.2.3 Development of the medical device

In 2021 the digital service was developed using a co-development approach including various stakeholders (21, 22). In total 9 workshops were conducted with researchers, product developers, designers, and health care professionals along with numerous short meetings in smaller groups in-between the workshops. Supplement 2 lists the involved stakeholders and figure 3 shows an overview of workshop themes and major decisions throughout the co-development phase. The COM-B system proposing capability, opportunity, and motivation as conditions for behavior served as a structural framework for the workshop discussions (25). The process of tailoring functions and features in the app was guided mainly by the Social Cognitive Theory (26) and the Transtheoretical Model of Change (27). After the development and prototype testing the Behavior Change Technique Taxonomy v1 (28, 29) was applied to label the functions that were finally included in the digital service. Thus, the use of behavior change techniques allows the included functions to be evaluated as mediators, compared to other studies, and included in meta-analyses. The included functions and behavior change techniques are described in supplement 4.

Figure 3. Main discussed contents of workshops with scientific advisory board during the development phase.

### 3.3. Pre-clinical testing

A pilot study evaluating the feasibility of the digital service LongLife Active was completed in August 2022. The pilot study aimed to optimize the service to become usable and acceptable based on users' opinions. The subjects tested the service for three months. Validated questions on usability and acceptability of various functions were integrated into the service (30, 31) and engagement with the digital service have been evaluated by analysing analytics. The subjects were encouraged to leave continuous comments and feedback on the app by texting or speaking through a think-aloud function. Individual interviews and focus group discussions were arranged at the end of the test period to collect viewpoints on the digital service from users, health coaches, and program developers. A manuscript is in progress.

A total of 105 people showed an interest in participation, of these 55 participants signed up to use the digital service. Five participants dropped out due to various reasons, leaving 50 active users throughout the 12-week testing period. Most participants were recruited via social media (94%), most were female, and the majority were between the ages of 50-64. Regarding engagement with the app functions, 25 of the participants actively set at least one goal for behavior change. Most popular topic was physical activity, followed by mental balance and diet. The average goal success for both daily and weekly goals was 55.1%. In all, 39 participants had at least one activity from week 1 in the intervention period registered. In terms of engagement on a weekly basis with regards to registering activities, as expected fewer activities were registered later on in the intervention period; the number of activities registered dropped consecutively after week 5. Just over 80 activities were registered in week 1, with an increase to around 140 activities and staying steady at this level in weeks 2-5. This number then dropped to 60 activities in week 9 and further dropped to 20 activities in week 12. The most common (median) number of activities registered was 3. Across the 12-week intervention 14 participants wrote comments in the community function and 20 participants had at least one coaching session.

The response rate of the initial questionnaire was 64%. On a question about the initial screening questions, 59% agreed that these questions were relevant to their lifestyle. Concerning assistance with goal setting, 31% found that the LongLife Active service was good/very good in helping them to concrete their goals and 22% experienced the service was bad/very bad in concreting their goals. The goal setting function has been improved fundamentally since. In all, 69% felt good/very good and 40% very good about leaving personal or sensitive information in the service, and only 3% (1 participant) felt bad about this.

The response rate of the questionnaire covering the perceived usability of the service collected by the System Usability Scale (SUS) at week 3 was 30%. The overall SUS score was 50.0, which is an OK rating, one that is slightly below the average (32). Acceptability was assessed by the Mobile Application Rating Scale (MARS) at the same time point. The score is out of 5 and indicate overall app quality. The overall MARS score was 3.27, which is considered to be acceptable (3). The mean scores for all the sections were: engagement = 2.97, functionality = 2.83, aesthetics = 3.29 and information quality = 4. No adverse events or dissatisfaction were reported.

The seemingly low response rates to the questionnaires and reduced engagement over time were expected. The findings from the pilot study, especially the individual interviews, have powerfully guided further development and optimization of the digital service and the design of the clinical evaluation.

Another pilot study including 20 individuals with type 2 diabetes who tested the device for 1 months was completed in April 2023. The participants gave constructive feedback on the usability and value of the device. Twelve of the participants were interviewed and their comments have been very useful for adapting and optimizing the device, especially the action plan and goal setting functions. A manuscript describing the findings is in progress.

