#### 4.6 Rationale for the benefit-risk ratio.

Expected benefits of the medical device outweighs the potential risks. On the first hand, there are anticipated benefits on well-being and behavioral outcomes. In addition to these anticipated benefits, previous studies have reported further empowerment and health literacy benefits of digital

interventions in relation to self-management. Examples of benefits are improved decisions making skills concerning the own health, perceived facilitation of self-management, an understanding of self-monitoring readings, increased awareness, a sense of control over a condition, and improved motivation to continue self-management activities (35). In this study the subjects will set self-identified goals and decide for themselves of a weekly plan for how to reach the goals in their own pace. Suggestions, encouragement, inspiration, and feedback will be tailored to preferences and identified needs of each individual. These are factors that potentially lead to improved empowerment and health literacy.

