#### 5.2 Secondary objectives

II) To study internalization and implementation factors such as reach and dose of the medical device across 6 months.

III) To explore the impact of three different levels of digital support for healthy habits on reaching self-identified goals, dietary and physical activity habits, and mental health after 6 months.

IV) To explore determining response of sociodemographic factors in meeting the self-identified goal, dietary and physical activity habits, mental health, and well-being.

V) To evaluate the intended mediators (engagement with the service, improved motivation, self-efficacy, and reduced perceived barriers) of the medical device on achieving the self-identified goal, improved dietary and physical activity habits, mental health, and well-being.

VI) To explore what app functions and features mediate improvements of the medical device on behavior change, mental health, and well-being.

VII) To explore the engagement of using the digital service and adherence to behavior change across 24 months.

VIII) To explore the patterns of achieving the self-identified goal, change in motivation, dietary and physical activity habits, mental health, and well-being across 24 months.

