#### *Goal achievement*

Reaching the self-identified goal will be evaluated by collecting information on number of days/week the self-identified goal was met during the past month. Confidence for reaching the goal will also be asked for on a scale 1 low confidence to 6 high confidence.

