|                              | Days/week the self-identified goal was met during the past month | Analytics                                       | x                  | x | x | x | x  | x  | x  |
| Mediators                    |                                                                  |                                                 |                    |   |   |   |    |    |    |
|                              | Self-efficacy                                                    | The General Self-Efficacy scale (S-GSE)         | x                  |   | x | x | x  | x  | x  |

|                                                      |                                                                                                            |   |   |   |   |   |   |
|------------------------------------------------------|------------------------------------------------------------------------------------------------------------|---|---|---|---|---|---|
| Motivation                                           | Readiness to change questionnaire (RTCQ)                                                                   | x | x | x | x | x | x |
|                                                      |                                                                                                            |   |   |   |   |   |   |
| Barriers                                             | CDC Road to health barriers                                                                                | x | x | x | x | x | x |
| Lifestyle habits                              |                                                                                                            |   |   |   |   |   |   |
| Physical activity                                    | Daily number steps from the app**                                                                          | x | x | x | x | x | x |
|                                                      | Daily minutes in different intensities and sedentary behavior                                              | x |   |   | x | x | x |
|                                                      | Questions from the National Board of Health and Welfare on active transport and physical activity at work. | x |   |   | x | x | x |
| Dietary habits                                       | Questions from the National Board of Health and Welfare and additional questions on plant-based food.***   | x |   |   | x | x | x |

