### 7.4 Sample size calculation

The endpoint well-being will be assessed using the WHO-5 Well-being Index (34). In our pilot study the mean score at baseline was 55. The instrument has to our knowledge not been applied on a general Swedish population. In Danish general population surveys, the mean WHO-5 score was 60-70 ( $sd=19.0-19.9$ ) (36, 47, 48). A change of 10-20 points in WHO-5 has been proposed as a clinically relevant change (36, 49). In up-scaled interventions 60% lower effects are expected (50). We therefore aim at a difference of 12 points in the score between intervention groups and control group as well as between baseline and 6 months. A fluctuation in well-being is considered normal (36), subjects with well-being score  $>70$  are not expected to improve and will be excluded from the analysis. In the pilot study 21% of participants reached 70 points at baseline.

Desirable sample size was calculated to detect an effect of 12 points (36, 51) based on the assumption of two-tailed testing, an alpha error  $\alpha=0.05$  and power  $1-\beta=0.90$  and  $sd=19.9$  (48). To detect a medium standardised effect size of 0.5 (Cohen's d) for the primary outcome well-being at 6 months a sample size of at least 25 subjects per group is recommended. Expected drop-out rate due to withdrawal and lost to follow-up at six months is 75 %. Based on the expected drop-out rates and on excluding 20% from the analysis due to baseline score  $>70$ , we need to recruit at least 500 subjects to assure 25 subjects in each intervention arm. In the control group we assume subjects to be excluded based on using a digital product for behavior change and strive to include 200 subjects.

The secondary outcomes are exploratory due to the person-centred design of the service. The subjects will set individual goals and possibly change goals during the intervention. Likewise, habits and behavior change are largely changeable due to circumstances. The current research is not immense enough to guide a decision for minimal expected effects when individual goals are set (e.g., reducing weekly servings of red meat). A larger sample size than what is required for the primary

endpoint well-being is desired. Similarly, the secondary analyses of mediating factors and responsiveness require a large sample size. We therefore aim to include 5000 subjects.

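### Goal achievement is counted in days per week without scaling to the goal's own target, so equal success can score differently for daily and non-daily goals

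*Protocol*

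**What the plan says.** Protocol section 6.3.2, under Goal achievement, evaluates the self-identified goal by the "number of days/week the self-identified goal was met during the past month". Table 1 repeats the unit ("Days/week the self-identified goal was met during the past month"), gives app analytics as the source, and schedules it at months 0, 1, 3, 6, 12, 18 and 24. Neither place relates the count to how often the goal was meant to be met.

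Three other places bear on what kinds of goal exist:

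- Section 3.3, on the pilot completed in August 2022: "The average goal success for both daily and weekly goals was 55.1" per cent. Daily and weekly goals were summarised together as a success percentage. The same section says of the period after the pilot: "The goal setting function has been improved fundamentally since".
- Section 7.4, on this trial, explains that the literature cannot guide a choice of "minimal expected effects when individual goals are set (e.g., reducing weekly servings of red meat"). The example is a per-week target.
- Section 4.6 says that subjects in this study "decide for themselves of a weekly plan for how to reach the goals in their own pace".

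Section 1.6 lists goal achievement among the secondary (intermediate) endpoints. Section 5.2 uses it in objective III ("To explore the impact of three different levels of digital support for healthy habits on reaching self-identified goals") and in objectives IV, V and VIII. In section 5.3, hypothesis 4 names it as a mediator.

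**The concern.** A count of days per week has a natural meaning for a goal that is due every day: seven is full success. For a goal due three times a week, full success is three if each session day counts. A weekly total, such as a limit on servings, is not met on particular days at all; it is met or missed once the week is over. The score then carries two things at once, the goal's target frequency and how well the user did against it.

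The analyses that use the score compare people and times at which the goal mix may differ. The support levels are chosen and paid for by users or their employers (section 3.1), so nothing balances goal type between them. Section 7.4 expects that subjects may change goals during follow-up, so a user who moves from a daily to a weekly goal with unchanged success could appear to decline. A larger sample does not remove this.

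**Working it through.** **Inputs**

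- Success rate s = 0.551 (section 3.3). This is a pooled pilot figure. No numerators, denominators or separate rates by goal type are given, so it cannot be reproduced and serves only as an illustration.
- Scale: days per week, maximum 7 (section 6.3.2 and Table 1).
- Days credited per met week for a weekly goal, c: not stated. Assumption: c lies between 1 and 7.

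**Score at equal success**

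- Daily goal: 7 × s = 7 × 0.551 = 3.86 days/week.
- Weekly goal: c × s.
  - c = 1: 1 × 0.551 = 0.55
  - c = 3: 3 × 0.551 = 1.65
  - c = 7: 7 × 0.551 = 3.86

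The ratio of daily to weekly score at the same success is 7/c. It is 7 when one day is credited and 1 when all seven are.

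**Ordering of a fully met weekly goal against a half-met daily goal**

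- Half-met daily goal: 7 × 0.5 = 3.5.
- Fully met weekly goal: c. It lies below 3.5 for c = 1, 2 or 3, and above 3.5 for c = 4 to 7.

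**Effect of goal mix on a group comparison**

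If two groups have the same success s, and the share of daily goals differs by d, the difference in mean score produced by the mix alone is d × s × (7 − c). The documents give no goal-mix data. Taking d = 0.20 purely as an assumption:

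- c = 1: 0.20 × (3.857 − 0.551) = 0.66 days/week
- c = 3: 0.20 × (3.857 − 1.653) = 0.44 days/week
- c = 7: 0

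**On a scale relative to the goal's own target**, a fully met weekly goal is 100%, a half-met daily goal is 50%, and both goal types score 55.1% at the pilot's success rate. The dependence on c disappears.

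**The case against.** The best case for leaving the text alone has four parts.

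First, the sentence that names daily and weekly goals describes the 2022 pilot version, and the goal-setting function was reworked afterwards. This stands as a limit: the goal types in the current app are inferred, not stated. The inference still has support within this trial, because section 7.4 offers a weekly target as its example of an individual goal. The weekly plan in section 4.6 is weaker support, since a weekly plan can serve a daily goal.

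Second, question wording and derivation details belong to the Case Report Form (supplement 6), which is not shown and may contain a crediting rule. That is possible. But the protocol itself fixes the unit, twice, and a rule elsewhere would have to be reconciled with it.

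Third, the goal mix and its difference between groups are unknown, so the size of any distortion is unknown. This stands; the 0.44 and 0.66 above are arithmetic on an assumed mix.

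Fourth, section 7.4 declares the secondary outcomes exploratory, and the mixed model in section 7.3 does not list goal achievement among its outcomes. This limits the consequences. However, the mediation analyses in section 7.3 do use goal achievement, and so do the objectives.

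A reader might go further and infer that a fully met weekly goal always scores below a half-met daily one. The documents do not support that. It is true if a met week earns one to three days and false if it earns four or more, and no rule is given.

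**Conclusion.** The point holds as a weakness in how the endpoint is defined. The days/week count is not scaled to the goal's target and does not fit goals that are not daily. At an illustrative 55.1% success, a weekly goal scores anywhere from 0.55 to 3.86 days/week against 3.86 for a daily goal, depending on a convention that the protocol does not state. Only at the upper end, with all seven days credited, do the mean scores agree.

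This rests on non-daily goals still being available in the trial version of the app, which section 7.4 suggests but does not establish. Actual bias also requires the goal mix to differ between groups or to change over time; the documents give no data on that. The analyses exposed are those of objectives III, IV, V and VIII and hypothesis 4. The primary WHO-5 endpoint and its sample size are not touched.

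**What to change.** In section 6.3.2 and Table 1, replace the days/week count with the percentage of the goal's own target occasions met in the past month:

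- daily goals: days
- goals set for a number of times a week: planned sessions
- weekly totals: weeks

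Average this over the user's active goals, which also settles how to score a user with more than one. Use the same variable wherever goal achievement is an outcome or a mediator.

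The cost is one changed definition and a matching edit to the Case Report Form; no additional subjects are needed. The pilot already reported a success percentage covering both goal types, but its method is not described. The sponsor must therefore confirm that the current app analytics store each goal's target frequency. If they do not, that field has to be added.

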## 4. Benefits and risks of the investigational device, clinical procedure, and clinical investigation

Risk management activities are planned based on ISO 14155:2020 and will be performed throughout the clinical investigation. A risk-benefit analysis is described below as well as in the supplement 3. The subjects are informed of risks and mitigation of risks upon consenting.

### 4.1 Anticipated clinical benefits

The primary expected clinical benefit of regular use of and engagement with the digital service is improved well-being, else, the anticipated benefits depend on what behavior the subject chose to focus on. Eating and physical activity habits, sleep, stress, and exhaustion symptoms will be assessed as secondary outcomes. Additional benefits for the individuals that are expected to follow the anticipated improved physical activity levels and eating habits, although not tracked during the investigation, are reduced depressive symptoms and reduced cardiometabolic risk factors (e.g. overweight and obesity, blood lipids, metabolic control, blood pressure).

